### Informants

The following informants will be considered for assessment: unblinded clinician, blinded clinician, parent/caregiver, patient, and teacher.

The unblinded clinician will be a member of the project staff who is involved in diagnostics or in therapy (but not in the family being assessed). He/she may be aware of the treatment condition and the time of the assessment, although efforts will be undertaken to blind the raters. The blinded clinician will also be a member of the project staff, and will be aware of neither the treatment condition nor the time of the assessment. To ensure blindness of the clinical rating of the primary outcome, the parent interviews will be videotaped and subsequently rated. Any information in the video material that may disclose the treatment condition or the measurement point (e.g., T1, T2, T3, T4) will be hidden for the rating. The parent may be the biological parent or the guardian of the child, and will be involved in the treatment. The caregiver may be an educator in residential care or a foster parent. The patient is the child participating in the study/treatment. The teacher is the child’s schoolteacher, preferably the class teacher with the main responsibility for the child’s school routine.

### Outcomes

#### Primary outcome

The primary efficacy outcome is the blinded clinician-rated AD symptom score of the child based on parent/caregiver interview at T1-T4. To date, there is a lack of validated measures on AD [6]. Therefore, the DADYS-PI will be developed by another subproject of the ADOPT consortium (ADOPT Epidemiology, in cooperation with ADOPT Treatment) before the start of the trial, based on a pre-version of DADYS-PI which will be psychometrically analyzed in a clinical sample. The pre-version includes items based on the Emotion Regulation Checklist (ERC) [79], the Diagnosis Checklist for Disruptive Behavior Disorder from the German Diagnostic System for Mental Disorders in Children and Adolescents (DISYPS-III) [80], the Affective Reactivity Index (ARI) [81], the Parent Proxy Scale [82], and the Pediatric Anger Scale from the Patient-Reported Outcomes Measurement Information System [83].

Blinded clinician ratings based on parent/caregiver interviews will be used as the primary outcome, since these ratings should be less biased compared to parent ratings and self-ratings of the child. The items of DADYS-PI are scored from 0 (not present) to 3 (very strong). These items are added up to a total score, representing the extent of AD symptoms of the child.

#### Secondary outcomes

The secondary endpoints are summary scores/scale scores of the respective items. The secondary outcomes listed below will be evaluated at T1-T4, unless otherwise noted.

The secondary outcomes are (1) psychosocial impairment of the child due to AD symptoms in blinded clinical rating as well as patient, parent/caregiver, and teacher rating, (2) patient-, parent/caregiver-, teacher- and clinician-rated AD symptoms of the child, (3) patient-, parent/caregiver- and teacher-rated symptoms of ADHD and ODD/CD, (4) other comorbid conditions (e.g., anxiety, depression) assessed by parent/caregiver ratings and teacher ratings, (5) psychological well-being in patient and parent/caregiver rating, and (6) parent / caregiver satisfaction with the treatment.

Psychosocial impairment of the patient due to AD symptoms will be measured by the functional impairment scale of the new version of the DISYPS-III [80]. The items are based on the definition of functional impairment in DSM-5 and assess social impairment in relationships with adults and other children, and impairment in academic functioning. The reliability and validity of the scale have already been established in German samples [80]. The items will be integrated into the clinical interview (DADYS-PI) and into the questionnaires for patient, parent/caregiver, and teacher rating (DADYS questionnaires).

Patient-, parent/caregiver- and teacher-rated AD symptoms of the child will be measured by newly developed questionnaires (DADYS questionnaires). Additionally, there will be a clinical rating of AD symptoms of the child based on a clinical interview with the child (DADYS-CI). The instruments will be developed by another subproject of the ADOPT consortium (ADOPT Epidemiology, in cooperation with ADOPT Treatment) before the start of the trial, based on a pre-version of the DADYS questionnaires and DADYS interviews, which will be psychometrically analyzed in a clinical sample. The DADYS instruments include items based on the ERC [79], FBB-SSV/SBB-SSV from the DISYPS-III [80], ARI [81], the Parent Proxy Scale [82] and the PROMIS Pediatric Anger Scale [83].

Comorbid symptoms of ADHD and ODD will be assessed in patient and parent/caregiver rating using the respective rating scales (Self-Rating Scale for ADHD, SBB-ADHS; Self-Rating Scale for ODD and CD, SBB-SSV; Rating Scale for ADHD, FBB-ADHS; Rating Scale for ODD and CD, FBB-SSV) based on DSM-5 criteria within the DISYPS-III [80]; reliability and validity as well as sensitivity to change of these scales has already been proven in German samples [80]. Teachers will rate comorbid symptoms of ADHD and ODD using selected items of a screening questionnaire (Rating Scale for Screening; FBB-Screen) of the DISYPS-III [80].

Further comorbidities will be assessed in parent/caregiver and teacher rating with the German version of the Child Behavior Checklist (CBCL/6-18R) [84] and the Teacher Report Form (TRF/6-18R) [85]. Three subscales will be used (Anxious/depressed, Attention problems, Aggressive behavior).

Child symptoms of attachment disorders/posttraumatic stress disorders will be assessed in parent/caregiver rating using the respective scales of the DISYPS-III (Rating scale for attachment disorders, FBB-BIST; Rating scale for trauma- and stress-related disorders, FBB-TBS) based on DSM-5 criteria [80].

The KIDSCREEN questionnaires [86] measure subjective health and well-being of children and adolescents as rated by patients (KIDSCREEN-10-Index) and parents/caregivers (KIDSCREEN-27).

For the assessment of satisfaction with the interventions at T2 (ADOPT Online) or at T3 (ADOPT Treatment), specific parent/caregiver satisfaction rating scales have been developed, based on the Client Satisfaction Questionnaire (CSQ) [87].

#### Predictors/moderators of treatment outcome on AD symptoms and impairment

As predictors/moderators of treatment outcome on AD symptoms and impairment, the following variables will be analyzed: (1) gender, (2) age of patients and parents/foster parents, (3) recruitment process (community cohort vs. outpatient sample; in ADOPT Online/ADOPT Treatment); (4) chronicity of AD symptoms, (5) severity of AD symptoms, (6) severity of comorbid symptoms, (7) AD symptoms and other psychopathology of the participating parent/foster parent, (8) positive and negative parenting practices, (9) receipt of social welfare assistance by the family, (10) socioeconomic status of the family/foster family, (11) early childhood neglect of the patient, (12) adverse childhood experiences of the patient, (13) family climate according to the child’s perception, (14) social support and (15) personal resources of the child. These parameters will be assessed at T1 and/or at T2. Additionally, (16) the profile of usage of the online tool (ADOPT Online) as well as (17) the implementation of treatment modules (ADOPT Treatment/ADOPT Institution) will be assessed and analyzed as predictors of treatment outcome in the intervention groups, along with (18) treatment adherence and (19) treatment fidelity in ADOPT Treatment/ADOPT Institution, both rated by the therapist, (20) the current mood of the patient (measured with the momentary assessment function of the therapy app), and (21) behavior, thoughts, emotions, and reactions of the child in therapy-relevant difficult situations (measured with the video diary function of the therapy app).

Sociodemographic variables (e.g., gender of the patient, age of patients and parents/foster parents, receipt of social welfare assistance by the family/foster family, socioeconomic status of the family/foster family) will be assessed via parent/caregiver interview at T1.

The chronicity of AD symptoms of the child will be assessed with the DADYS-PI (see above) at T1.

The severity of AD symptoms will be assessed at T2 in blinded clinical rating as well as patient, parent/caregiver and teacher rating using the DADYS-PI/questionnaires (see above).

The severity of comorbid symptoms of the child will be assessed at T2 using the SBB-ADHS/−SSV, FBB-ADHS/−SSV, CBCL/6-18R, and TRF/6-18R (see above). Additionally, at T1, comorbid symptoms will be assessed in clinical rating, based on parent/caregiver interview before treatment using a structured screening interview which is part of the comprehensive Structured Interview for Children and Adolescents according to ICD-10 and DSM-5 from the DISYPS-III (DISYPS-III-ILF) [[name] & [name], in preparation]. ILF-SCREEN is a semi-structured interview that is used to screen for core symptoms of ADHD, ODD, anxiety disorders, depression, autism and problems with contact behavior in children. For use in ADOPT Treatment, items concerning developmental and excretion disorders will be excluded. If ILF-SCREEN provides evidence of comorbid symptoms, additional scales from the DISYPS-III clinical interviews, corresponding to these symptoms, will be employed (ILF-External, ILF-Internal, ILF-Kontakt).

AD symptoms of the parent/foster parent participating in the treatment of the child will be measured at T1 via self-rating using the Aggression/Hostility subscale from the German Brief Symptom Checklist (BSCL) [88]. The scale consists of five items that are rated by the participating parent.

Psychopathology of parents and foster parents will be assessed at T1 with the 9-item self-report short version of the Symptom Checklist (SCL-K-9) [89].

Positive and negative parenting practices will be assessed at T1-T4 via rating of the participating parent/caregiver using the German Questionnaire for Positive and Negative Parenting (FPNE) [90], which measures positive parenting (e. g. reinforcing and supportive) and negative parenting (e. g. harsh and inconsistent discipline).

Early childhood neglect and traumatic events of the patient will be assessed at T1 via parent/caregiver questionnaire using a modified version of the Symptom Checklist for Attachment Disorders from the DISYPS-III [80] and the Symptom Checklist for Posttraumatic Disorders from the DISYPS-III [80].

Family climate will be assessed at T1 in parent/foster parent rating using the Family Climate Scale [91].

Social support will be assessed at T1 in parent/caregiver rating using the Social Support Scale (SSS) – Short Version [92].

Personal resources of the child will be assessed with three items from the Self-Efficacy Scale [93], one item from the Bern Well-Being Questionnaire [94] and one item from the Sense of Coherence Scale [95]. The items were modified for the assessment in parent/caregiver rating.

The profile of usage will be analyzed to identify the frequency and duration of usage and the selection of ADOPT Online modules.

Implementation of treatment modules, treatment adherence and treatment fidelity will be rated by the therapists in the THOPAS group after each session of treatment.

For the assessment of the child’s current mood using the momentary assessment function of the therapy app, the child will be asked to indicate how he/she is feeling three times per day over three five-day periods (at the beginning, in the middle and at the end of treatment). Different basic emotions will be presented and the child can choose between the emotions and indicate how strong the emotion/s is/are perceived to be at the specific moment. Additionally, four items from the patient-rated DADYS questionnaire (see above) will be included in the momentary assessment function.

For the assessment of behavior, thoughts, emotions, and reactions of the child in therapy-relevant difficult situations using the video diary function of the therapy app, the child will be asked to “tell” the app about a specific situation and to record it using the video function. The child will then be asked to indicate the specific behavior, thoughts, emotions and reactions that occurred in the situation.

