### Participant timeline

For ADOPT Online and ADOPT Treatment, the individual study duration per patient is 19 months. Measurements will take place according to a specified schedule. Immediately after the initial investigation (T0, screening), the first measurement (T1) will occur, which involves an examination of inclusion and exclusion criteria. For parents of patients randomized to the experimental group at T1, ADOPT Online will then be carried out over a period of 12 weeks. Measurement T2 will take place 13 weeks after T1. Families that were randomized to TAU after T1 will be offered ADOPT Online at T2. Non-responders to ADOPT Online at T2 (significant symptoms of AD at T2 as rated by the clinician based on parent interview) will subsequently be randomized to either THOPAS or TAU, which will each be carried out over a period of 32 weeks. T3 will occur 32 weeks after T2. The follow-up measurement T4 will take place 32 weeks after T3. Thus, for all patients in ADOPT Online, there will be four study visits (T1-T4). For non-responders to ADOPT Online, who continue treatment in ADOPT Treatment, there will be 24 additional study visits (24 behavior therapy sessions including one intermediate measurement).

For ADOPT Institution, the individual study duration per patient is 16 months. Measurements will take place according to a specified schedule. Immediately after the initial investigation (T0, screening), the first measurement (T1) will occur, which involves an examination of inclusion and exclusion criteria. Children with AD will subsequently be randomized to either THOPAS or TAU, which will each be carried out over a period of 32 weeks. T2 will take place 32 weeks after T1. The follow-up measurement T4 will be conducted 32 weeks after T2. Thus, for all patients in ADOPT Institution, there will be three study visits (T1-T3). For children randomized to THOPAS, there will be 24 additional study visits (24 behavior therapy sessions including 1 intermediate measurement).

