#### Analysis of primary endpoint

The primary (full) analysis set is derived from the ITT principle (all patients randomized with a valid baseline assessment: ADOPT Online/ADOPT Institution: T1/ADOPT Treatment: T2 and at least one follow-up measurement). The primary outcome measures “change in AD symptoms from T1 to 13 weeks post-randomization (T2)” (ADOPT Online), “change in AD symptoms from T2 to 32 weeks post-randomization (T3)” (ADOPT Treatment) and “change in AD symptoms from T1 to 32 weeks post-randomization (T2)” (ADOPT Institution) will be evaluated by an ANCOVA, with fixed effects baseline, study center, gender and treatment arm and corresponding marginal means and contrast tests (type II sums of squares). Interactions of study center and gender with treatment arm will be explored. Data from study centers with low recruitment (i.e., < 10 patients) will be pooled. The potential clustering of observations of participants by therapist or center will be investigated using multilevel modelling. Multiple imputation approaches will be taken to assess the robustness of the results. Specifically, missing values will be separately imputed by type assuming mixtures of missingness-not-at-random patterns [102]. Imputation data sets will be post-processed by multiplication with factors and addition of offsets (tipping point analysis) [103]. Proxy measures will be taken into account to ameliorate the effects of attrition.

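### AD and comorbid severity as moderators are timed at T2 for all three trials, but T2 is the pre-randomisation visit only in ADOPT Treatment; in ADOPT Online and ADOPT Institution it is the primary endpoint visit

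*Protocol article*

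**What the plan says.** In the Protocol article, the section on predictors/moderators of treatment outcome lists 21 variables. Items 5 and 6 are the severity of AD symptoms and the severity of comorbid symptoms. For the first 15 items it gives one general timing: "These parameters will be assessed at T1 and/or at T2". It then times individual variables. Chronicity, sociodemographic data and parental psychopathology are placed at T1. For AD severity, measured with the DADYS-PI and questionnaires, it says "The severity of AD symptoms will be assessed at T2 in blinded clinical rating as well as patient, parent/caregiver and teacher rating". For the comorbidity rating scales it says "The severity of comorbid symptoms of the child will be assessed at T2", and it adds a clinical screening interview at T1. Neither T2 statement names a subproject, although other items in the section do. The Background poses the profile and moderator questions for all three trials.

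Under Primary outcome: "The primary efficacy outcome is the blinded clinician-rated AD symptom score of the child based on parent/caregiver interview at T1-T4".

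Under Analysis of primary endpoint, the endpoints are:
- ADOPT Online: "change in AD symptoms from T1 to 13 weeks post-randomization (T2"
- ADOPT Institution: "change in AD symptoms from T1 to 32 weeks post-randomization (T2"
- ADOPT Treatment: "change in AD symptoms from T2 to 32 weeks post-randomization (T3"

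**The concern.** A moderator answers the question of which children, as they were before treatment, gain more or less from it. It therefore has to be measured before randomisation, or at least be beyond the reach of treatment. The visit label T2 does not mean the same thing in the three trials, yet the severity variables carry that one label throughout. In ADOPT Online and ADOPT Institution it points to the assessment at which the effect of treatment is read.

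An analyst who followed the text there would stratify or adjust on a result of treatment. For the DADYS-PI, the moderator and the final value of the endpoint would be the same number. At stake are the severity part of the moderator question and, to a lesser degree, the psychopathological-profile question in those two trials.

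**Working it through.** **1. Which visit is T2?** The plan states no figure on this point, so the main check is to compare sections.

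| Trial | Timing of T2 (Participant timeline) | Baseline in primary analysis | T2 relative to randomised treatment |
|---|---|---|---|
| ADOPT Online | "Measurement T2 will take place 13 weeks after T1", after a 12-week intervention | T1 | after |
| ADOPT Institution | 32 weeks after T1, after 32 weeks of THOPAS or TAU | T1 | after |
| ADOPT Treatment | before the 32-week THOPAS or TAU period | T2 | before |

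The T2 timing of severity suits the third row only.

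**2. What would follow in the first two rows?** Inputs from the section Sample size: effect sizes d = 0.378 (Online) and d = 0.6 (Institution); group sizes 331 and 66 (Online, before attrition is added); 140 children at T2 in Institution, taken as 70 per arm. The T1–T2 correlation ρ is not given; 0.3 to 0.7 is assumed, with unit SD at both visits. Negative change means improvement.

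*T2 severity as covariate, T1 not in the model.* Within an arm, the slope of change (T2 − T1) on T2 is cov(T2 − T1, T2)/var(T2) = 1 − ρ. The arms differ by −d in mean change and by −d in mean T2. The adjusted arm effect is −d − (1 − ρ)(−d) = −ρd, a loss of the fraction 1 − ρ. A simulation (400 runs per setting, severity-by-arm term included, no true interaction) agrees:

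| Trial | ρ | Severity at T1, simulated arm effect | Severity at T2, −ρd | Severity at T2, simulated |
|---|---|---|---|---|
| Online (true −0.378) | 0.3 | −0.376 | −0.113 | −0.119 |
| | 0.5 | −0.382 | −0.189 | −0.202 |
| | 0.7 | −0.382 | −0.265 | −0.269 |
| Institution (true −0.60) | 0.3 | −0.593 | −0.180 | −0.168 |
| | 0.5 | −0.614 | −0.300 | −0.308 |
| | 0.7 | −0.594 | −0.420 | −0.412 |

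Severity at T1 recovers the true effect. Severity at T2 loses 30% (ρ = 0.7) to 70% (ρ = 0.3) of it.

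*Both T1 and T2 DADYS-PI as covariates.* Change = T2 − T1 is then an identity: coefficients −1 for T1, +1 for T2 and 0 for arm, with R² = 1. This needs no assumed correlation.

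*The interaction.* With no true interaction, the simulated interaction test at the 5% level rejected in 2.0% to 6.8% of runs with T2 severity and in 4.0% to 7.8% with T1 severity. So this simple setting does not create false moderators. A true one can be misread, however. Suppose ρ is 0.3 in the intervention arm and 0.5 under TAU, again with unit SDs:
- Moderator at T1: slopes of change are ρ − 1, that is −0.7 and −0.5; interaction −0.7 − (−0.5) = −0.2 (more benefit with higher initial severity).
- Moderator at T2: slopes are 1 − ρ, that is 0.7 and 0.5; interaction 0.7 − 0.5 = +0.2 (apparently less benefit with higher severity).

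The sign reverses.

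**The case against.** The best defence is that the T2 wording was carried over from ADOPT Treatment, where it is correct, and that "These parameters will be assessed at T1 and/or at T2" was meant to point to each trial's own pre-treatment visit. The section Concomitant care uses a similar T1/T2 shorthand for pre-treatment assessment, and the primary analysis assigns the baselines correctly. That may well be the intention, but the general sentence assigns no visit to any trial, and the specific sentences that follow it name T2 for severity. They also include caregiver ratings; under Informants, the caregiver is an educator in residential care or a foster parent, which describes the ADOPT Institution population.

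The defence is right on several further points, and they rule out stronger readings that a reader might infer:

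- **That the planned moderator models are known to condition on the outcome and return a zero arm effect.** The article gives assessment times and names interaction and simple-slope methods, but no equation. The identity needs T1 and T2 DADYS-PI together as covariates for T1–T2 change. It does not extend to the questionnaires or comorbidity scales, and a fit with no residual would be noticed.
- **That the profile question will be answered wrongly in two of the three trials.** The article's example contrasts high with low ADHD. The T1 interview screens for ADHD, and the ADHD and ODD/CD scales are among the secondary outcomes collected from T1 onwards.
- **That the primary result is at risk.** The primary ANCOVA uses the correct baseline in each trial.
- **That every post-randomisation variable must go.** Usage, adherence and fidelity are planned deliberately as predictors within the intervention groups.

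T2 severity in ADOPT Online can also legitimately predict later course, although the text does not restrict it to that use.

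**Conclusion.** The point holds as a wrong or at best unassigned visit for one group of variables. For AD severity and the comorbidity rating scales, the article names a visit that is pre-randomisation in one trial and the post-treatment endpoint in the other two, and nothing elsewhere in it settles which visit applies there. Following the text would attenuate the arm effect and could distort or reverse severity interactions in ADOPT Online and ADOPT Institution.

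The 30% to 70% attenuation rests on assumed correlations, unit SDs and a model without T1; the sign reversal rests on assumed arm-specific correlations. The degenerate fit rests on no assumed value, but only on a model that the article does not specify. The consequence is most direct for the DADYS-PI and milder for comorbidity. It is confined to the predictor/moderator analyses. The point should be corrected before those analyses are run, but it does not threaten the main conclusions.

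**What to change.** State in the section on predictors/moderators, and carry into the analysis plan, that AD severity and comorbid severity used as moderators (treatment-by-severity interaction) are taken from each trial's pre-randomisation visit: T1 in ADOPT Online and ADOPT Institution, T2 in ADOPT Treatment. These are the baselines already defined for the primary analysis.

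Add two limits. Post-randomisation variables such as usage, adherence and fidelity serve only as predictors within the intervention arm. T2 severity in ADOPT Online serves only as a predictor of later course at T3/T4, not as a moderator of the randomised comparison.

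The cost is a few lines of text. The DADYS-PI, the questionnaires and the comorbidity scales are already scheduled at T1, so there is no added assessment and no effect on sample size.
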